| *Screening*  After patient is consented to the study, a baseline blood test (32mls, including pregnancy test, Hepatitis B test, Hepatitis C test, full blood count, liver function test and renal function test) and chest X-Ray will be conducted during the baseline visit to assess for eligibility prior to enrolment to the treatment phase. Additional research blood (14.5mls, 1 tablespoons) will be collected at this baseline visit for research purposes. Patient may be exempted from chest X-Ray and/or blood test if patient has done the same test within 30 days.  Baseline demographics and relevant clinical variables of patients will be collected. The following demographic and clinical variables will be collected: age of presentation, pre-menopausal or post-menopausal status, parity / breastfeeding status, concomitant rheumatic conditions, personal or family history of tuberculosis, smoking or alcohol intake, presenting complaint, unilateral or bilateral involvement, affected quadrant of the breast, duration of symptoms and previous antibiotics prescription for treatment of IGM.  Information on comorbidities will be evaluated to ensure suitability for both treatment arms prior to recruitment. Examples include drug allergies, plans for pregnancy, ongoing infection, previous history of cancer, previous tuberculosis, epilepsy, diabetes, hypertension, kidney, liver, cardiac problems, osteoporosis, glaucoma, peptic ulcers, previous side effects to either prednisolone or methotrexate.  If patient fulfilled all the eligibility criteria after screening assessment, she will be randomised to either of the treatment arm.  If patient did not meet the full eligibility criteria (eg. Pregnant, hepatitis carrier or abnormalities in renal or liver panels), she will not proceed to the treatment phase. The data collected and additional blood samples will be kept for analysis.  *Treatment Phase*  Patient will be scheduled to attend a clinical visit (T_0_) to either breast or rheumatology clinic if she meets all eligibility criteria for the initiation of treatment dose. There will be a window period of ± 7 days for this clinical visit. Patient is required to complete a pre-treatment quality of life online survey (approximately 10-15 minutes).  Patient will be scheduled for blood test (8mls, 0.5 tablespoons) and clinical visits to either breast or rheumatology clinic at the 1^st^ (T_1_), 2^nd^ (T_2_), 3^rd^ (T_3_) and 6^th^ (T_4_) month to assess their signs and symptoms, and drug compliance. There will be a window period of ± 14 days for each of these clinical visits. Additional research blood (14.5mls, 1 tablespoons) will be collected on the 1^st^ (T_1_) and 6^th^ (T_4_) months.  Patients are required to undergo a breast ultrasound to assess for their radiological response during the 3^rd^ (T_3_) clinical visit. A window period of ± 14 days will be applicable. The initial measurement of the breast lesion or mass will be recorded in three dimensions – i.e. anteroposterior, superior-inferior, mediolateral measurements. If complete clinical and radiological complete response has been achieved on the 3^rd^ (T_3_) visit, the doctor will discontinue the drug in a safe manner and no further breast ultrasounds will be required. If the patient’s symptoms or signs have not resolved by the 3^rd^ (T_3_) clinical visit, patient’s drug dosage will be assessed by the rheumatologist and treatment may be continued up to the 6^th^ (T_4_) month period and a repeat breast ultrasound will be required at the 6^th^ (T_4_) month. If symptoms have not resolved by the 6^th^ (T_4_) month of clinical visit, the patient’s drug dosage may be up-titrated or will be given an addition of a second therapy, i.e. combination therapy of steroid and methotrexate may be used. For clinical visits mention above, it will coincides with standard care visit.  During the clinical visits, Tingting Hu et al’s “M- score” will be adopted to grade the severity of the disease. M score is being calculated during clinical visits for IGM patients regardless of trial status for objective follow up. This is a common practice. For this study, the score will be administered by their attending healthcare professional (not limited to breast surgeons, investigators, or breast care nurses).  The M-score will be the sum of the following:  1) Mass score  2) Erythema score  3) Fistula score  4) Pain score  5) Quality-of-life (QoL) score  The scoring criteria were defined as follows:  1) Mass score: 0 for the absence of mass by palpation; 1 for mass ≤3 cm by palpation; 2 for mass >3 cm by palpation.  2) Erythema score: 0 and 2 for the absence and presence of erythema, respectively  3) Fistula: 0 and 2 for the absence and presence of fistula, respectively  4) Pain Score: 0 for Visual Analogue Score (VAS) 0-2; 1 for VAS 3-5; 2 for VAS 6-10  5) QoL score: 0 for absence of effects on QoL; 1 for mild effects on QoL, where the patient does not require medical assistant; 2 for serious effects on QoL, where the patient requires medical assistant  The total M-score ranges between 0 and 10 and serves as a quantitative and objective measurement of the severity of the symptoms.  The primary endpoint will be the clinical complete response (cCR) rate, which is defined as the proportion of patients who have an M-score of ≤ 1 at ≤1 years after treatment.  The secondary endpoints will be as follows:   - - The time to cCR, defined as the median time to cCR post randomisation.   - The treatment failure (TF) rate, defined as the proportion of patients with TF at 1 year post randomisation. The TF status will be defined as follows:     - If the patient has an M-score ≥6 before randomisation, TF is defined as the M-score remaining at ≥6 at 1 month post randomisation.     - If the patient has an M-score between 4 and 5 before randomisation, TF is defined as the M-score remaining at ≥4 and never being lower than 4.     - If the patient has an M-score <4 at baseline but never reaches cCR after randomisation, TF is defined as the M-score being >5 at the follow-up and remaining above 5 for one month. - Relapse rate, which is defined as the proportion of patients who have M-score >4 among the patients who achieved CR.   Throughout the course of the study, there are possible flares and relapse of the disease. Flares will be defined as any increase in M-score or lesion size on ultrasound whilst on therapy. While relapse will be defined as recurrence of symptoms or signs of IGM in the breast after previously experiencing complete resolution following therapy. If relapse occurs, patient will restart the same treatment arm for 6 months.  In the event of flares, blood test (8mls, 0.5 tablespoons) and additional research blood (14.5mls, 1 tablespoons) will be collected and the allocated treatment for the patient will be up-titrated by the doctor. In event of relapse, treatment for the patient will be reinitiated as per the allocated arm.  Additional research blood samples collected during the trial will be used for gene expressing profiling to identify unique patterns of gene expression that can be used to diagnose IGM and predict its treatment response.  Regardless of treatment arm, patient will be monitored by either breast surgeon or rheumatologist. Surgeons will assess for eligibility into trial, clinical reviews, and ultrasound breasts interpretation. Rheumatologists will be monitoring for drug side effects and titration if required. In event of failure of medical therapy, surgeons will have to intervene accordingly for aspiration or surgical drainage. In the event where patients require aspiration or surgical drainage during the study, methotrexate or prednisolone should be continued unless there is evidence of sepsis. The frequency of aspiration or surgical intervention will be recorded as events during the study.  Whenever the disease has been resolved during the study period, the balance medication and/or packaging will be retrieved to do medication accounting and checking for adherence to assigned treatment arm.  If side effects were to develop, doctors will evaluate the severity of the side effects and withdraw the patients from the trial if needed. |  |

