| Investigational Product (IP):   1. Prednisolone: 20mg/day. Y.S.P Prednisolone 5mg by Y.S.P. Industries (M) Sdn Bhd 2. Methotrexate: 15mg/week. Emthexate 2.5mg by TEVA Czech Industries S.R.O   Auxiliary Product (AP):   1. Omeprazole: 20mg/day. Zenpro Omeprazole 20mg by XEPA-SOUL Pattinson (Malaysia) Sdn Bhd 2. Folic acid: 5mg/day. Folic Acid Sunward tab 5mg by Sunward Pharmaceutical Pte Ltd |  |
| Storage and Drug Accountability |  |
| The PI and study team will be responsible to maintain the storage in IMU and drug accountability for all the trial product. | |
|  | |
| **TREATMENT** | |
| Rationale for Selection of Dose | |
| For safety reason, the dose of drugs used in this study is standard dosage in accordance with the approved labels. | |
| Study Drug Formulations | |
| All drugs dispensed to the patients are in tablet (methotrexate, folic acid, prednisolone) form and capsule form (omeprazole) for oral consumption. | |
| Study Drug Administration |  |
| 1. 20 mg of prednisolone daily for first 2 weeks, followed by tapering doses of 15mg daily over 2 weeks, then 12.5 mg daily for 2 weeks, proceeding to 10 mg daily for 2 weeks, subsequently taking 7.5mg daily for 2 weeks, and lastly 5mg daily for 2 weeks (refer to Figure 2). 20mg of omeprazole is to be taken together with prednisolone. 2. 15mg of methotrexate to be taken once a week for a month, and increased to 20mg of methotrexate to be taken once a week for another two months. 5mg of folic acid is to be taken together with methotrexate.   PI or Co-Is may increase the methotrexate dosage from 20mg to 25mg depending on patients’ responses to the drug and doctor’s discretion. PI or Co-Is may increase 5mg folic acid intake up to 6 times a week (except the day of taking methotrexate) to mitigate methotrexate’s side effects, if needed. |  |
| Specific Restrictions / Requirements |  |

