| De-identified blood samples will be analysed and stored in NUH Tissue Repository. Recruitment and follow-up survey data will be collected electronically via NUHS REDCap. Only study team members with delegated rights will be able to access the data under the supervision of PI and Site-PI. All survey data will be collected electronically via FormSG. A copy of de-identified data will be stored in a secured server at NUH. |  |
|  |  |
| **SAMPLE SIZE AND STATISTICAL METHODS** |  |
| Determination of Sample Size |  |
| The prevalence rate of IGM in NUH is currently at 10 to 15 patients per year. Based on a stepped rule of thumb, a minimum sample size of 30 will provide at least 80% power to detect a medium standardised effect size of between 0.3 to 0.7 based on a randomised two-group comparison (Machin et al, 2021). Assuming a 20% attrition rate, the sample size required for this study is 36 patients. This will be rounded up to a sample size of 40 patients over a period of 36 months. |  |
| Statistical and Analytical Plans The primary outcome of 6-month clinical or radiological complete response will be compared between arms using Chi-square test. The effect estimate will be quantified in terms of difference in proportion as well as relative risk (RR) and their associated 95% confidence interval (CI). The secondary outcomes of time-to clinical or radiological response and time-to-relapse will be evaluated via the Kaplan-Meier method. The differences in survival curves will be compared using log rank test, with the effect estimate quantified in terms of hazard ratio and its 95% CI. The primary analysis of this trial will be based on Intention-to- Treat (ITT). A Per Protocol (PP) analysis will be performed on all patients who have completed 6 months of treatment regimen as a sensitivity analysis.  Chi square test will be used to evaluate the proportion of side effects and requirement for percutaneous or surgical intervention during treatment between arms. Modified Poisson regression will be used to identify clinical or biomarkers that are associated with treatment response and quantify the effect in terms of RR.  Patient reported outcomes will be reported via a survey on FormSG, conducted online. The questions will be adapted from SF36 V1 Singapore version and EORTC-BR23. Below are the domains to be compared:   - - General Health   - Physical Health   - Mental Health   - Body Image   - Sexual Image   - Breast Health |  |
| **ETHICAL CONSIDERATIONS** |  |

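### The per-protocol set requires 6 months of treatment, but the planned course is about 3 months and full responders stop at month 3, so membership depends on the outcome

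*Protocol*

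**What the plan says.** Protocol section 11.2 makes ITT the primary analysis and names one sensitivity analysis: "A Per Protocol (PP) analysis will be performed on all patients who have completed 6 months of treatment regimen as a sensitivity analysis". The outcome concerned is given in the same section: "The primary outcome of 6-month clinical or radiological complete response will be compared between arms using Chi-square test".

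Treatment length is described elsewhere:

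- **Prednisolone (section 8.3).** The taper opens with "20 mg of prednisolone daily for first 2 weeks, followed by tapering doses of 15mg daily over 2 weeks", passes through 12.5 mg and 10 mg for two weeks each, and closes with "subsequently taking 7.5mg daily for 2 weeks, and lastly 5mg daily for 2 weeks".
- **Methotrexate (section 8.3).** One month at the starting dose, then "increased to 20mg of methotrexate to be taken once a week for another two months". Section 1.2 gives different methotrexate doses but the same duration. The dose conflict is a separate matter and does not affect this point.
- **Month-3 decision (section 6.3, Treatment Phase).** "If complete clinical and radiological complete response has been achieved on the 3^rd^ (T_3_) visit, the doctor will discontinue the drug". Where symptoms or signs persist at that visit, continuing to month 6 is permitted but not required.
- **Relapse (section 6.3).** The patient restarts the same arm for 6 months.

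**The concern.** A per-protocol set should hold the patients who did what the protocol asked. Here a patient who takes every dose, reaches clinical and radiological complete response at month 3 and stops as directed has about 3 months of treatment. On the literal wording she is outside the set. The main way in is to be unresolved at month 3 and to continue. Membership therefore depends on an outcome measured after randomisation and closely tied to the endpoint being analysed.

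Two consequences follow. The response rate in the set is too low in both arms. In addition, if one arm works faster, more of its successes are removed. Section 2.1 hypothesises exactly that: a shorter time to response on methotrexate. The only sensitivity analysis named in section 11.2 could then disagree with the ITT result for reasons unrelated to adherence.

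**Working it through.** **Step 1: can the 6-month figure be reproduced from the regimen?**

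- Prednisolone: 6 steps × 2 weeks = 12 weeks (section 8.3).
- Methotrexate: 1 + 2 = 3 months (sections 1.2 and 8.3).

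Neither gives 6 months. Month 6 is reached only by optional continuation after month 3 or, possibly, by re-treatment after relapse.

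**Step 2: who can be in the set on the literal wording?**

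| Status at month 3 | Section 6.3 | In the set? |
|---|---|---|
| Clinical and radiological complete response | Drug stopped | No, even if fully adherent |
| Complete response on one criterion only | Stop rule not met; may continue | Possibly |
| Unresolved, continues | Treated to month 6 | Yes |
| Unresolved, does not continue | Treatment ends | No |
| Relapse after response | 6 months' re-treatment | Not settled |

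**Step 3: effect on the comparison.** The protocol gives no month-3 response rates, so all rates below are assumed. Let *a* be the proportion who respond fully and stop at month 3, and *b* the proportion of the rest who respond between months 3 and 6. The planned 20 per arm comes from section 5.1. Assume full adherence, that month-3 responders all stop and remain responders at month 6, and that all others continue to month 6. Then:

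- ITT response = a + (1 − a)b
- Per-protocol (PP) response = b
- PP size per arm = 20(1 − a)

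For a = 60% v 30% and b = 40% in both arms:

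- ITT: 0.60 + 0.40 × 0.40 = 0.76, against 0.30 + 0.70 × 0.40 = 0.58. The difference is +18 points and the relative risk 0.76/0.58 = 1.31.
- PP: 40% v 40%, in 20 × 0.40 = 8 and 20 × 0.70 = 14 patients. The difference is 0 and the relative risk 1.00.

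Other assumed rates, faster arm first where the arms differ:

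| a | b | ITT | PP n | PP | Effect |
|---|---|---|---|---|---|
| 30% v 30% | 40% v 40% | 58% v 58% | 14 v 14 | 40% v 40% | Level understated, difference unbiased |
| 50% v 30% | 40% v 40% | 70% v 58% (+12) | 10 v 14 | 40% v 40% (0) | Difference erased |
| 75% v 50% | 40% v 40% | 85% v 70% (+15) | 5 v 10 | 40% v 40% (0) | Difference erased |
| 60% v 40% | 50% v 67% | 80% v 80% (0) | 8 v 12 | 50% v 67% (−17) | Difference created |
| 60% v 30% | 30% v 40% | 72% v 58% (+14) | 8 v 14 | 30% v 40% (−10) | Sign reversed |

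In the fourth row the later conversion follows from equal month-6 rates: (0.80 − 0.60)/0.40 = 0.50 and (0.80 − 0.40)/0.60 = 0.67, or 4/8 v 8/12 patients. The last two rows both have lower later conversion in the faster arm. With equal later conversion the PP difference is exactly 0.

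**The case against.** **The phrase may mean the protocol-directed course through month 6.** On that reading it includes the stop-or-continue decision at month 3. Section 6.3 describes the month-6 visit under the treatment phase and places only month 12 under follow-up, which gives some support. Figure 1, as far as its layout can be read, puts month 6 in follow-up. The reading is possible, but nothing states that a month-3 stop counts as completion, and two analysts could build different sets from the sentence.

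**The set does not exclude every success.** A reader might infer that it contains only non-responders. The documents do not support that. The stop needs both clinical and radiological complete response while the endpoint needs either, so a single-criterion responder at month 3 may stay. Patients who respond between months 3 and 6 also stay. And because continuation is optional, some unresolved patients leave the set too. These points stand and limit the size of the effect. They do not restore the adherent dual responders, who are the clearest successes.

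**It is a sensitivity analysis in a pilot of 40 patients.** This stands. Section 3.5 also keeps persistently non-compliant patients in an ITT analysis, so the primary estimate, test and interval are untouched.

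**The definition could be left to the statistical analysis plan.** Detail could be, but section 11.2 already states a rule, and that rule conflicts with the treatment rules in the same document.

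**Conclusion.** The per-protocol rule is wrong as written, and the issue is moderate. The mismatch between 6 months and a 12-week or 3-month course comes straight from the text, as does the exclusion of adherent patients who reach both responses by month 3. Understated response follows whenever such patients exist. Distortion of the arm difference also requires the arms to differ in speed of response or in later conversion. Under the assumptions in the working, a true 18-point ITT difference can vanish, or 17 points can appear where ITT shows none. These figures illustrate the mechanism and are not predictions: optional continuation, single-criterion responders and relapse would all change them.

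Two stronger conclusions should not be drawn. A reader might infer that the set would reverse the trial's finding, but faster response alone only erases the difference; a change of sign also needs lower later conversion in the faster arm, for which the protocol gives no evidence. A reader might also infer that the main result is compromised, but it rests on ITT and is not affected.

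**What to change.** In section 11.2, replace the 6-month treatment requirement with a definition on these lines: the per-protocol set comprises eligible randomised patients who adhered to the allocated, protocol-directed course up to month 6 and whose 6-month clinical or radiological endpoint was assessed; a protocol-directed stop at month 3 for complete response counts as completing the course.

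Three details should go with it:

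- **Adherence.** Judge it by the compliance checks at visits, including months 3 to 6 for patients who continue, and by medication accounting where available. Sections 6.3 and 6.3(iv) state medication accounting only at disease resolution and at a discontinuation visit, so it cannot be the sole source. Say that dose changes allowed by the protocol are not deviations, and how re-treatment after a relapse before month 6 is classed.
- **Endpoint assessed.** Do not require one particular component. For month-3 dual responders section 6.3 says "the doctor will discontinue the drug in a safe manner and no further breast ultrasounds will be required", so a clinical assessment at month 6 must be enough. Otherwise the same patients are lost by another route.
- **Treatment length.** Reconcile sections 6.3, 8.3 and 11.2 so that they describe one course. Which length is intended is for the investigators to state.

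The cost is a sentence or two in the protocol, with no new visit, test or change to treatment. It should be settled before outcome data are examined by arm.

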| This is a prospective pilot randomised trial to study the effectiveness of prednisolone versus methotrexate in achieving clinical or radiological complete response for women with IGM. The study will be conducted in NUH. This study evaluates the effectiveness of each drug in terms of clinical and/or radiological response, time to resolution as well as total number of flares over a period of one year follow-up. This study can potentially identify a more effective treatment with fewer side effects for women with IGM as well as personalize drug choices for patients who are at risk of frequent flares. |  |
| **HYPOTHESIS AND OBJECTIVES** |  |
| Hypothesis |  |
| The hypothesis is that methotrexate has a higher 6-month clinical or radiologically complete response with lesser side effects than prednisolone. The time to clinical or radiological response is shorter in the methotrexate arm compared to prednisolone arm. Relapse and time to first relapse is lower and longer in the methotrexate arm compared to prednisolone arm. |  |
| Primary Objectives |  |
| The primary objective is to evaluate the 1) Proportion of patients who achieved clinical or radiological complete response at 6 months 2) Time to clinical response and time to radiological response, and 3) Proportion of patients with relapse in one year within affected breast between each arm. |  |
| Secondary Objectives |  |
| The secondary objectives include evaluation of:   1. Side effects 2. Frequency of percutaneous or surgical intervention required 3. Potential biomarkers that may predict response to treatment: eg IL-6, CRP and neutrophil to lymphocyte ratio (NLR) 4. Patient reported outcome measures 5. Validate survey instrument for IGM patients |  |
| Potential Risks and benefits |  |
| End Points – Efficacy |  |
| Benefits expected for the patient are the total remission of IGM or reduced relapsed/flare of IGM. |  |
| End Points – Safety |  |

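### Interventions are to be counted over the study, but the only stated test is of a yes/no proportion in an undefined window, during treatment

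*Protocol*

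**What the plan says.** - **Objective (section 2.3).** The second secondary objective is "Frequency of percutaneous or surgical intervention required".
- **Data (section 6.3).** "The frequency of aspiration or surgical intervention will be recorded as events during the study". Follow-up lasts one year; the design rationale in section 1.2 likewise refers to the "total number of flares over a period of one year follow-up".
- **Analysis (section 11.2).** "Chi square test will be used to evaluate the proportion of side effects and requirement for percutaneous or surgical intervention during treatment between arms". No other analysis of interventions is given.
- **Time on drug (section 6.3).** On complete clinical and radiological response at month 3, "the doctor will discontinue the drug in a safe manner and no further breast ultrasounds will be required". Otherwise "treatment may be continued up to the 6^th^ (T_4_) month period". If symptoms persist at month 6, the "drug dosage may be up-titrated or will be given an addition of a second therapy", with no end date stated. Also, "If relapse occurs, patient will restart the same treatment arm for 6 months".

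**The concern.** Between objective and analysis, two things change. The measure goes from a number of events to any versus none, and the period goes from the study to *during treatment*. The first change drops repeat procedures, which are part of the burden that the objective sets out to describe. The second ties the comparison to a period that the protocol does not define and that, on one reading, is itself shaped by outcomes compared between the arms.

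At stake is whether a secondary result answers its own objective, and whether a difference or its absence can be read as an effect on the need for procedures. Section 11.2 names the test, the measure and the window, so this is not a detail left open for a later analysis plan.

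**Working it through.** The protocol gives no rate, effect size or power for interventions, so there is no figure of its own to reproduce. The check compares the texts and adds two illustrations.

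**1. Measure.** Take 20 patients per arm (section 5.1). Suppose 8 patients in each arm need a procedure, one each in the first arm and three each in the second.
- Proportions: 8/20 = 40% in both arms, so chi-square = 0.
- Counts: 8 × 1 = 8 against 8 × 3 = 24 procedures.

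The planned test cannot see this difference; the recorded data can.

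**2. Window read as time on drug.** From section 6.3:
- complete response at month 3: about 3 months;
- not resolved at month 3: up to 6 months;
- not resolved at month 6: possibly longer, with no stated end;
- relapse after stopping: a further 6 months, so a month-3 responder can reach 3 + 6 = 9 months.

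Illustration, with all rates and shares assumed: the same constant rate λ per month in both arms, a share p stopping at month 3 and the rest at month 6, no relapse.

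P(any) = p(1 − e^(−3λ)) + (1 − p)(1 − e^(−6λ))

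With λ = 0.10, 1 − e^(−0.3) = 0.259 and 1 − e^(−0.6) = 0.451.
- p = 0.75: mean window 0.75 × 3 + 0.25 × 6 = 3.75 months; P(any) = 0.75 × 0.259 + 0.25 × 0.451 = 30.7%.
- p = 0.45: mean window 0.45 × 3 + 0.55 × 6 = 4.65 months; P(any) = 0.45 × 0.259 + 0.55 × 0.451 = 36.5%.

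That is 31% against 37% with no difference in rate. Other assumed values:

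| λ per month | 40% v 60% stop at month 3 | 30% v 70% | 20% v 80% |
|---|---|---|---|
| 0.05 | 21.1% v 18.7% | 22.3% v 17.5% | 23.5% v 16.3% |
| 0.10 | 37.4% v 33.6% | 39.4% v 31.7% | 41.3% v 29.8% |
| 0.20 | 60.0% v 55.0% | 62.5% v 52.5% | 64.9% v 50.1% |

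The artificial difference runs from 2.4 to 14.9 percentage points.

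**3. Relapse can undo or reverse the gap.** The windows of 3.75 and 4.65 months differ by 0.90. If a share r of the month-3 responders in the faster arm relapse and complete six more months within the year, that arm gains 0.75 × r × 6 = 4.5r months. With no relapse in the other arm, the gap closes at r = 0.90/4.5 = 20% (3 of 15 responders) and reverses above that.

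**4. Window read as the scheduled phase.** It is then the same calendar period in both arms and the artefact in step 2 is zero. Its end is still unclear. Figure 1 (section 4) appears to put month 6 under follow-up. Section 6.3 describes the month-6 visit under the treatment phase and only the month-12 visit under follow-up. Procedures after that end are recorded but not tested.

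**5. After the fix.** From randomisation to month 12, planned exposure is 20 × 12 = 240 patient-months in each arm, and equal rates give equal expected counts and proportions.

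**The case against.** **A reader might infer that the better arm is watched for less time, so the test is biased in a known direction.** The documents do not support that. *During treatment* may mean the scheduled phase, which is equal in both arms. On the on-drug reading, relapse lengthens the window again. The protocol hypothesises faster response and less relapse on methotrexate, which would both shorten time on drug in that arm, but that is what the trial is testing, and more responders also means more patients who can relapse.

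**The illustration assumes an unlikely null.** Section 6.3 links aspiration and drainage to failure of medical therapy, so responders should have a lower rate than non-responders. An arm with more responders would then be expected to need fewer procedures in truth. This stands: the percentages show a mechanism and are not an estimate. Even taken as given, 31% against 37% is about 6.1 against 7.3 patients of 20. The uncorrected chi-square test would reject in about 7% of trials, against about 5.3% with equal proportions.

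**Procedures off drug are not lost.** They are recorded, and many later ones would fall in a re-treatment period. What remains outside an on-drug test is narrower, for example procedures in patients taken off drug for adverse reactions but kept for outcome data (section 3.5).

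**Frequency can mean how many patients needed a procedure.** That is possible from section 2.3 alone. Recording frequency as events in section 6.3 favours the count, and no count summary is stated.

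**Conclusion.** The mismatch holds. The objective and data collection concern the frequency of events over the study; the stated analysis is any/none in an undefined treatment window. On either reading of that window, repeat procedures and some recorded procedures drop out of the only stated comparison. Unequal exposure between arms is possible on the on-drug reading only; neither its direction nor its size can be taken from the protocol. The range of 2.4 to 14.9 points rests on assumed equal constant rates, assumed stopping shares and no relapse.

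This is a minor point: a secondary outcome in a 40-patient pilot, with no bearing on the primary comparison or the sample size.

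**What to change.** In section 11.2, for interventions:

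1. Replace the treatment window with randomisation to month 12, in all randomised patients. This fits the intention-to-treat principle already stated there.
2. Keep the any/none comparison over that window.
3. Add the number of interventions per patient by arm, with a rate ratio and 95% CI using robust standard errors, presented as an estimate.
4. Optionally show the same summaries cut at month 6 as support.

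Figure 1 and section 6.3 should also be reconciled on where the treatment phase ends. The window for side effects need not change: on-treatment reporting is conventional, and follow-up after month 6 is lighter (no scheduled blood tests at month 12, and that visit may be a teleconsultation).

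**Cost.** Some wording and one simple model, on events already to be recorded. The interval will be wide at 20 per arm, and a few patients with many procedures can drive the rate ratio, so it should not replace the any/none comparison. The 12-month comparison includes any combination therapy given after month 6, so it compares treatment policies and not the two drugs alone; the month-6 cut helps to show this.
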